## Abstract

**Background:**

Despite the effective scale-up of HIV testing and treatment programs, only 75% of people living with HIV (PLWH) globally know their status, and this rate is lower among men. This highlights the importance of implementing HIV testing and linkage interventions with a high uptake in this population. In a cluster randomized controlled trial conducted in Kenya between 2013 and 2015, we found that assisted partner services (APS) for HIV-exposed partners of newly diagnosed PLWH safely reached more HIV-exposed individuals with HIV testing compared with client referral alone. However, more data are needed to evaluate APS implementation in a real-world setting.

**Objective:**

This study aims to evaluate the effectiveness, acceptability, fidelity, and cost of APS when integrated into existing HIV testing services (HTS) in Western Kenya.

**Methods:**

Our study team from the University of Washington and PATH is integrating APS into 31 health facilities in Western Kenya. We are enrolling females newly diagnosed with HIV (index clients) who consent to receiving APS, their male sexual partners, and female sexual partners of male sexual partners who tested HIV positive. Female index clients and sexual partners testing HIV positive will be followed up at 6 weeks, 6 months, and 12 months postenrollment to assess linkage to care, antiretroviral therapy initiation, and HIV viral load suppression. We will evaluate the acceptability, fidelity, and cost of real-world implementation of APS via in-depth interviews conducted with national, county, and subcounty-level policy makers responsible for HTS. Facility health staff providing HTS and APS, in addition to staff working with the study project team, will also be interviewed. We will also conduct direct observations of facility infrastructure and clinical procedures and extract data from the facilities and county and national databases.

**Results:**

As of March 2020, we have recruited 1724 female index clients, 3201 male partners, and 1585 female partners. We have completed study recruitment as well as 6-week (2936/2973, 98.75%), 6-month (1596/1641, 97.25%), and 12-month (725/797, 90.9%) follow-up visits. Preliminary analyses show that facilities scaling up APS identify approximately 12-18 new HIV-positive males for every 100 men contacted and tested. We are currently completing the remaining follow-up interviews and incorporating an HIV self-testing component into the study in response to the COVID-19 pandemic.

**Conclusions:**

The results will help bridge the gap between clinical research findings and real-world practice and provide guidance regarding optimal strategies for APS integration into routine HIV service delivery.

**International Registered Report Identifier (IRRID):**

DERR1-10.2196/27262

## Introduction

The HIV epidemic continues to cause significant morbidity and mortality, disproportionately affecting sub-Saharan Africa (SSA), where most HIV infections occur [1]. Approximately 65% of people living with HIV (PLWH) globally know their status, suggesting that expanding targeted testing strategies are needed to achieve the first 95 of the Joint United Nations Programme on HIV/AIDS ambitious testing, treatment, and viral suppression targets [2]. PLWH in SSA are largely diagnosed through facility-based HIV testing; however, testing coverage is lacking and insufficient to curb the HIV epidemic, particularly in men and vulnerable populations [3]. Barriers to facility testing include distance, costs, and confidentiality concerns, which result in many PLWH presenting late for care when they are already symptomatic or at advanced stages of the disease [4,5].

Assisted HIV partner services—providers contacting and testing sexual and injecting partners of people diagnosed with HIV—can be an efficient strategy for diagnosing people with HIV, linking them to HIV care and prevention [6,7]. In 2016, the World Health Organization recommended offering assisted partner services (APS) to all PLWH to close the gap in HIV testing coverage [8], and these services are now rapidly scaling up globally. Partner contacting and testing can be conducted through (1) client referral—newly diagnosed individuals (index clients) are asked to notify their partners of exposure and encourage HIV testing; (2) provider referral—providers contact partners and offer testing while ensuring the clients’ confidentiality; and (3) contract referral—index clients and providers agree on a set amount of time for clients to notify partners, after which providers contact partners and offer testing [9]. In practice, APS are implemented as a combination of these options.

Clinical trials and demonstration projects of APS in SSA have found high HIV positivity (30%-63%) among sexual partners of index clients and high median CD4 counts at diagnosis, indicating that individuals are identified earlier in their disease course compared with those identified by facility-based testing [3,10-13]. Early case detection and linkage to care can improve clinical outcomes [11,14,15]. Mathematical modeling analyses indicate that APS are a cost-effective strategy for reducing HIV burden in SSA [16]. In addition, APS are an effective method to reach men through their HIV-positive female partners, as women are tested for HIV at higher rates than men [17]. Men in SSA are more likely to start antiretroviral therapy (ART) at advanced disease stages and consequently have poorer clinical outcomes compared with women [18,19]. Low male testing and treatment rates also serve to increase HIV transmission to their female partners.

Despite its demonstrated efficacy, scaling up APS presents challenges. The translation of findings from randomized controlled trials into real-world settings can be a challenge because of weaknesses in health system structures and differences in intervention delivery, monitoring, and available resources [20]. The implementation of science evaluations of APS offers a real-world approach using existing systems to scale up interventions. As a critical next step in bringing APS to scale in Kenya and across SSA, this study uses implementation science methods to assess the effectiveness and feasibility of APS and generates evidence to inform rapid and sustainable implementation across the region.

Our objective is to evaluate the effectiveness, feasibility, and cost of implementing APS integrated within routine HIV testing services (HTS) in Western Kenya, a region with high HIV prevalence (>15%) [21]. Specifically, we aim to (1) evaluate the effectiveness of integrated APS and (2) determine the integration, implementation fidelity, acceptability, demand, and costs of implementing APS. By identifying health facility and individual-level factors that influence the uptake of HIV testing, linkage to care, and fidelity to APS, we will evaluate how these factors inform the successful scale-up of APS in Kenya.

## Methods

### Study Design

This hybrid type 2 implementation science study [22] has two aims: (1) to determine the effectiveness of APS when integrated within routine HTS and (2) to evaluate the implementation of APS in these settings, including the integration, implementation fidelity, acceptability, demand, and costs of the intervention. The study leveraged existing integrated HIV prevention, care, and treatment platforms from the Afya Ziwani project, the existing President’s Emergency Plan for AIDS Relief–funded and PATH. PATH is a local nongovernmental organization in Western Kenya. HTSs are provided in facility and community settings, including *safe spaces* where DREAMS (Determined, Resilient, Empowered, AIDS-free, Mentored, and Safe) interventions are provided to vulnerable adolescent girls and young women.

The DREAMS program aims to reduce new HIV cases by providing girls and young women at the highest risk of HIV infection and their partners, families, and communities with a tailored, comprehensive, and evidence-informed HIV service package, including HTS. Afya Ziwani provides technical implementation support to health facilities that serve as sites for study enrollment. Nine safe spaces have been created within the catchment areas of health facilities that provide a variety of services, including HTS, by staff for adolescent girls and young women. Excluding the antenatal care clinics, around 50-80 persons test HIV positive each month in larger facilities and 10-20 in smaller facilities, with more than 50% of newly diagnosed individuals being female. In 2018, HIV prevalence in Homa Bay and Kisumu counties was estimated at 19.6% and 17.5%, respectively, in the general population [23]. Therefore, this is a high number of girls and women with HIV who are enrolled in health facilities and linked safe spaces. This study integrated APS into the existing infrastructure of Afya Ziwani in collaboration with county and subcounty health management teams in Homa Bay and Kisumu counties.

The study was approved by the ethics and research committee of Kenyatta National Hospital (P465/052017) and the University of Washington institutional review board (STUDY00002420). No payment was provided to the participants for their participation. Breaches in confidentiality, study protocol, or adverse events attributable to this study were reported to both ethics and research committees and institutional review boards. The findings of this study will be disseminated to the Kenya Ministry of Health (MOH) and Kenya National AIDS and Sexually Transmitted Infection Control Programme (NASCOP) through direct communication and technical working group meetings and to the greater scientific and public health community through national and international conferences and peer-reviewed manuscripts in academic journals.

#### Study Participants

We planned to enroll up to 8000 female index participants (girls and women who tested positive for HIV at the facilities) and 10,000 sexual partners across study sites. The target enrollment was 2000 in year 1 of the study and 3000 per year in years 2 and 3. The inclusion criteria for the index participants were (1) female, (2) testing HIV positive and not in care or on treatment, (3) aged ≥18 years or emancipated minor (girls aged ≥15 years who are married; pregnant; or have had a sexually transmitted infection, including HIV), (4) willing to participate in the study, and (5) willing to provide contact information of ≥1 sex partner. Pregnant women, those younger than 15 years, and individuals who reported intimate partner violence (IPV) within the past month of enrollment were excluded. History of IPV was determined using an IPV screening questionnaire that included questions about emotional, physical, and sexual violence (Multimedia Appendix 1). Male sexual partners of index clients who tested HIV positive also received APS and their other female partners were notified of their potential HIV exposure and offered HTS.

#### Study Procedures

##### Index Participant Recruitment and Enrollment

Recruitment of index participants occurred at the study sites. Females testing HIV positive at the participating sites were provided information on the study, including an overview of APS and study procedures in English or local languages (Swahili and Luo) by HTS providers. The HTS staff screened the interested participants for eligibility and were asked to provide written informed consent if eligible. Enrolled participants were interviewed using structured forms regarding their demographic characteristics, sexual behavior, substance use, HIV testing history, and the number of male sex partners in the past 3 years. HTS providers collected contact information for all male sex partners in the past 3 years and emphasized that all information would be kept confidential and that the index cases’ identities would not be revealed when contacting their partners.

##### APS Procedures

HTS providers called all elicited male sexual partners to inform them of their HIV exposure and offer HIV testing at the facility or a convenient location in the community. Initially, up to three attempts were made to notify the partners by phone; if unsuccessful, or if the female index client did not provide a phone number for the partner, HTS providers physically traced the partners in the community. If unsuccessful, two further attempts were made to notify the partners, either by phone or in-person. Partners were classified as lost to follow-up after six unsuccessful attempts or if a partner refused to meet with an HTS provider.

When implementing APS, HTS providers informed the partners of their potential HIV exposure without identifying the index participant. They asked the partners about their HIV testing history, provided HIV counseling, and offered HIV testing. Partners with a prior HIV diagnosis were asked about their current HIV care, and those who were out of care were counseled about the benefits and locations to access care. If a notification occurred over the phone, partners were encouraged to seek HTS at a study site or offered the opportunity for study staff to conduct a home-based HIV test. For partners who chose to seek HTS at a facility or safe space, the HTS provider who conducted the initial outreach generally contacted the partners via telephone to remind them of their testing appointment, rescheduled appointments as needed, conducted HTS, and documented test results, even if HTS was conducted at nonstudy sites. If HTS was completed at a nonstudy site by the partner, results were obtained via self-report. If a notification occurred as part of a home visit, partners were offered HTS after verbal consent per Kenya national guidelines [24]. When possible, HTS providers accompanied HIV-positive partners to the nearest HIV comprehensive care center for linkage to care.

##### Partner Participant Recruitment and Enrollment

Partners were aged ≥18 years. Recruitment and enrollment of partner participants took place during the tracing visit. Before testing for HIV, partners were invited to enroll in the study; however, they did not need to enroll to get tested. When possible, male partners who tested HIV positive were offered APS for their other female sexual partners.

##### Participant Follow-Up

HTS providers made phone calls to assess linkage to and engagement in care and ART initiation for index clients and partners with HIV at 6 weeks and 6 months postenrollment. At 12 months postenrollment, participants were asked to make a physical visit to the comprehensive care center for clinical care consultation and to conduct an HIV viral load test. For all follow-up timepoints, participants who were not reached after three attempts by phone were physically traced.

##### IPV Monitoring

Adolescent girls and women reporting IPV within the past month were excluded from participation and instead referred to IPV counseling and other support services, as needed. Those reporting that they had not experienced recent IPV but feared IPV and abuse from a partner were eligible for study participation but had the option to refuse both APS and study participation. They received instructions regarding confidential reporting to clinical providers and study staff, and case report forms documenting any IPV were completed by phone or in person, depending on their preference. We provided additional training on IPV counseling for study staff and ensured that resources had been identified at all sites to safely refer females who reported abuse or concern for their safety. Individuals experiencing IPV were excluded at enrollment to avoid any harm as a result of notifying their partners. However, if they reported IPV at a follow-up visit (after enrollment), they were followed to ensure that they were safe and referred to IPV services as needed. In addition, these data will be helpful in studying the safety of APS.

#### Outcomes

The effectiveness outcomes included (1) number of persons testing for HIV for the first time among all tested, (2) male partners who are newly diagnosed with HIV versus known to be living with HIV among all tested, (3) linkage to care and initiation of ART by 6 weeks and follow-up at 6 months for male partners with HIV and female index clients, and (4) suppression of plasma HIV RNA levels to <400 copies/µL at 12 months among male partners living with HIV and female index clients. We also monitor adverse events, including IPV and relationship dissolution.

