#### Data Analysis

We will use log-binomial regression with robust standard errors to assess the proportion of participants with the main outcomes of interest and use multivariate log-binomial and logistic regression to examine the potential predictors of outcomes of interest, including participant demographics, HIV testing history, sexual behavior, and location. We will conduct time trend analyses to examine the changes in proportions with outcomes of interest over time as the APS are scaled up.

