## Discussion

The Kenya MOH and NASCOP guidelines for HIV testing recommends voluntary APS implementation as part of routine HTS. This study is designed to assess how best to implement and scale up APS within public health settings in low-income countries such as Kenya. We have integrated study activities and follow-up visits into existing routine HIV testing, prevention, and care programs at participating sites to assess how APS functions at scale in a real-world setting.

With the current global goal of reaching 95-95-95 in HIV epidemic control, the pool of undiagnosed PLWH continues to decline, and APS are an effective modality for reaching those who are undiagnosed. This is especially true for certain subgroups, such as men, who are more likely to be missed by standard HTS. In addition, the study documents other aspects of APS implementation, such as cost, fidelity, and acceptability, which will inform a costed national scale-up of this modality. We sought to identify the most critical factors for successful APS implementation by rigorously documenting process outcomes such as provider elicitation rates and phone versus physical tracing outcomes. The study results will inform national and county-level approaches for scaling up APS to prioritize the critical factors for success. The elicitation and documentation of IPV in the study also provides insights into the safety of APS. In addition, those identified as probable or confirmed IPV cases through the study are referred to gender-based violence centers of excellence for appropriate care, following best practices.

The limitations of this study include that some key outcomes, including linkage to care and ART, are self-reported by participants. Furthermore, the proportion of index clients who were adolescents was low (11%). To overcome these challenges, we are assessing viral loads that are at 12-months post APS to objectively assess ART linkage and adherence. In addition, our study did not enroll clients who were men who have sex with men, who are a key population that should be targeted via APS; future work is warranted in this area. Finally, some of the findings regarding implementation fidelity, integration, acceptability, demand, and cost may not be generalizable to other settings outside Kenya.

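### The viral suppression cut-off is printed per microlitre, which makes it 400,000 copies/mL; the unit needs to be confirmed and corrected

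*Protocol article*

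**What the plan says.** The Outcomes section for the effectiveness aim lists, as its fourth outcome, "suppression of plasma HIV RNA levels to <400 copies/µL at 12 months", assessed in HIV-positive male partners and in female index clients. The measurement comes from the 12-month visit described under Participant Follow-Up, when participants attend the comprehensive care center in person "to conduct an HIV viral load test". That section names no threshold.

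The other references to this outcome also carry no number. The Methods part of the Abstract says that participants are followed "to assess linkage to care, antiretroviral therapy initiation, and HIV viral load suppression". The Discussion concedes that "some key outcomes, including linkage to care and ART, are self-reported by participants" and answers: "we are assessing viral loads that are at 12-months post APS to objectively assess ART linkage and adherence".

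The Data Analysis section for the same aim plans "log-binomial regression with robust standard errors to assess the proportion of participants with the main outcomes of interest", followed by regression models for predictors of those outcomes and analyses of time trends.

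**The concern.** The unit is the problem. A count per microlitre is 1000 times larger when expressed per millilitre, so the printed definition puts the line between suppressed and unsuppressed at 400,000 copies/mL. Because this is the only place where the article gives a threshold, a reader or analyst has nothing in it to set against the figure.

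The cut-off creates the binary event. It therefore determines the reported proportion suppressed, the event variable in the predictor models, and any time trend in suppression. The 12-month viral load also has a specific job: it is offered as the remedy for self-reported linkage and ART. A cut-off that many untreated people would meet weakens that remedy, because someone who reported starting ART but did not could still be recorded as suppressed.

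**Working it through.** **Inputs from the article**
- Cut-off: 400 copies/µL (Outcomes, effectiveness aim).
- Time and measurement: viral load test at 12 months (Participant Follow-Up).
- Analysis: proportion with the outcome (Data Analysis, effectiveness aim).

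**Input assumed, not in the article**
- Untreated viral load is log-normal, with log10 copies/mL having a mean of 4.0 to 5.0 and an SD of 0.7 to 1.1.

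**Step 1: unit conversion.** 400 copies/µL × 1000 µL/mL = 400,000 copies/mL. On the log10 scale this is 5.60, against 2.60 for 400 copies/mL. The difference is exactly 3.0 log10. This step needs no assumption.

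**Step 2: share of untreated people below each cut-off.** The formula is Φ((log10 cut-off − mean) / SD).

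| Mean, SD (assumed) | Below 400,000/mL (as printed) | Below 400/mL |
|---|---|---|
| 4.0, 0.7 | 98.9% | 2.3% |
| 4.0, 1.1 | 92.7% | 10.2% |
| 4.5, 0.9 | 89.0% | 1.8% |
| 5.0, 0.7 | 80.5% | 0.03% |
| 5.0, 1.1 | 70.8% | 1.5% |

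For example, with mean 5.0 and SD 1.1: (5.602 − 5.0) / 1.1 = 0.547, and Φ(0.547) = 0.708. The range is about 71% to 99% at the printed cut-off and about 0.03% to 10% at 400 copies/mL.

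**Step 3: effect on the reported proportion (illustration).** Suppose that 70% are treated with a viral load below 400 copies/mL and 30% are untreated.
- Mean 5.0, SD 1.1: 0.70 + 0.30 × 0.708 = 91.2% as printed, against 0.70 + 0.30 × 0.0146 = 70.4% at 400 copies/mL.
- Mean 4.0, SD 0.7: 0.70 + 0.30 × 0.989 = 99.7% as printed, against 0.70 + 0.30 × 0.0229 = 70.7% at 400 copies/mL.

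**Step 4: ability to separate the groups.** If all treated people are below 400 copies/mL, the treated-minus-untreated difference in the outcome at the printed cut-off is 100 − 98.9 = 1.1 to 100 − 70.8 = 29.2 percentage points. At 400 copies/mL it is 100 − 10.2 = 89.8 to 100 − 0.03 = 99.97 percentage points.

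The article derives no sample size or power from this threshold, so there is no planning figure to reproduce and none that changes.

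**The case against.** The strongest reply is that this is probably a one-character slip in a condensed article. The full protocol, laboratory forms and code are not shown and may all use copies/mL. The viral load itself is measured at the visit, so a wrong printed unit does not harm data collection, and the Results section reports no suppression figure based on it. All of this stands. It limits the likely damage and makes the repair cheap, but it does not make the published definition right.

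Four stronger readings are tempting, and the article does not support them.

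- **That the analysis has been, or will be, coded with the wrong unit.** Nothing in the article shows this. The consequences above are conditional on literal use of the definition.
- **That suppression would come out near 100% whatever the adherence, or that the outcome could not separate treated from untreated people at all.** Both depend on an untreated viral-load distribution that the article does not give. At the lower end of the assumed range, about 29% of untreated people would still lie above the cut-off. Poor separation is what the working shows.
- **That this is the only objective effectiveness outcome.** The outcome on new versus known diagnoses in male partners also rests partly on HIV test results, which the APS Procedures section says providers documented, with self-report for tests completed at nonstudy sites. The narrower statement holds: viral load is the stated objective check on ART linkage and adherence.
- **That the intended cut-off is certainly 400 copies/mL.** This is almost certainly so, but no section says it, and it should be confirmed.

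**Conclusion.** The definition is wrong as printed: the stated unit makes the threshold 1000 times higher than the same number per millilitre, and no other section corrects it. That part rests on unit conversion alone.

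The practical effect rests on two conditions: that the definition is applied literally, and that untreated viral loads lie in the assumed range. Under both, most untreated participants would count as suppressed, and the outcome would largely fail in the role that the Discussion gives it. The direction is the same for every combination tried; the exact size is not known from the article.

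This is more than a cosmetic slip because the figure is the decision threshold of a named effectiveness outcome. It should be corrected before the outcome is analysed.

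**What to change.** 1. Confirm the intended threshold and unit against the full protocol and the laboratory reports.
2. Correct the outcome definition accordingly, almost certainly to <400 copies/mL.
3. Check that the laboratory export and the code that derives the suppressed/unsuppressed variable use the same unit, and do so before the 12-month analysis.

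The cost is a one-word correction and one check of the derivation. No new data are needed. The article describes the remaining 12-month visits as still being completed, so the definition could be settled without reopening any result that it reports.
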